### Follow‐up

2.5

Follow‐up will be conducted at 1 month, and then every 1‐3 months following the ablation procedure with clinic visits. Patients will be scheduled examinations, including 12‐lead ECGs, 24 hour Holter recordings (3, 12, 24, and 36 months after the procedure), and/or ambulatory electrogram recorder (HCG‐801, OMRON Healthcare Co., Ltd). In patients with cardiac implantable electronic device, home monitoring will be adapted to facilitate the continuous monitoring of AF episodes. In patients without cardiac implantable electronic device, one‐channel electrocardiograms will be recorded twice daily for 1 year after the procedure except for the blanking period of the 90 days with the use of ambulatory electrogram recorder. Echocardiography and QoL questionnaires will also be obtained during the follow‐up (3, 12, 24, and 36 months after the procedure). LVEF will be recommended to be calculated during sinus rhythm. The QoL will be assessed by AFEQT questionnaires.^18^ All documented atrial tachyarrhythmias (ATs) lasting ≥30 seconds occurring outside the blanking period of 90 days will be considered as a recurrence. In the case of recurrences outside the after ablation blanking period, it will be recommended to perform a second catheter ablation. The sum of the durations of all episodes of ATs regardless of lasting ≥30 seconds or not, will be calculated and expressed as a percentage with respect to 24 hours to assess the AF burden in patients with cardiac implantable electronic device.

Adverse events (AE) will be collected during the study periods. An AE is defined as any untoward medical occurrence in a subject in this study, regardless of whether the causal relationship of the AE with the ablation procedure.

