#### Primary endpoint

2.7.1

The primary endpoint of this study is the occurrence of ATs at 1 year with a blanking period of 90 days after ablation.

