### Randomization and allocation factor

2.10

The CRABL‐HF will consist of 110 patients at multicenter in Japan. The patients will be registered and randomly assigned to either the CB ablation or RF ablation group with a 1:1 allocation. We will use the minimization method proposed by Pocock and Simon to allocate the patients with an in‐house validated mail‐based system. Randomization will be stratified by the LA diameter, which may influence the evaluation of the efficacy of the ablation procedure,^22^ providing a balanced treatment assignment in both cohorts (<50 vs ≥50 mm). The patients' group allocations will be revealed to the operator at least 1 day before the ablation procedure. The information regarding the number of allocated subjects in each group will not be disclosed to the principal investigator or investigator until the completion of the study.

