### Statistical analysis

2.12

Comparisons between the randomized groups will be performed on the basis of the intention‐to‐treat (ITT) principle. A per‐protocol basis analysis will also be performed to assess the robustness of the conclusions derived from the ITT basis analysis. The Kaplan‐Meier method will be used to estimate the survival curve, and the log‐rank test will be used to compare the curves between the groups for the time‐to‐event variables. Categorical variables will be analyzed using a chi‐square test or Fisher's exact test. Continuous variables will be presented as the mean ± standard deviation or median with the interquartile range (25th‐75th percentiles) and compared with the Student's t test or Wilcoxon rank‐sum test, as appropriate. A *P* value < .05 will be considered significant. Up‐to‐date versions of JMP (SAS institute) will be used to conduct analyses. The patient demographic data and outcome of catheter ablation in each group will be collected descriptively as presented in Tables 1 and 2.

**Table 1 joa312322-tbl-0001:** Patient characteristics at baseline

Age, years, n (%)
Male sex, n (%)
Height, cm
Weight, kg
NYHA functional class
History of a heart failure hospitalization
Number of heart failure hospitalizations
Blood pressure, mm Hg
Heart rate, /min
Duration of atrial fibrillation, months
Congestive heart failure, n (%)
Hypertension, n (%)
Diabetes mellitus, n (%)
Stroke and/or transient ischemic attack, n (%)
Structural heart disease, n (%)
Coronary artery disease
Valvular heat disease
Dilated cardiomyopathy
Hypertrophic cardiomyopathy
Others
Postopen heart surgery
CHADS_2_ score
CHA_2_DS_2_‐VASc score
Echocardiographic data
Left ventricular ejection fraction, %
Left atrial dimension, mm (%)
Left atrial dimension, <50 mm
Left atrial dimension, ≥50 mm
Computed tomography data
Pulmonary vein diameter, mm
Cardiac implantable electronic device
Pacemaker
ICD
CRT‐P
CRT‐D
History of anti‐arrhythmic drug use, n (%)
Disopyramide, n (%)
Cibenzoline, n (%)
Aprindine, n (%)
Pilsicainide, n (%)
Flecainide, n (%)
Propafenone, n (%)
Bepridil, n (%)
Sotalol, n (%)
Amiodarone, n (%)
Verapamil, n (%)
Beta‐blocker, n (%)
Digitalis, n (%)
Others, n (%)
Laboratory data

**Table 2 joa312322-tbl-0002:** The ablation procedure and complications

Procedure time (groin puncture to catheter extraction), min
Left atrial dwelling time
Fluoroscopic time, min
For cryoablation
Total freezing cycles, n
Total freezing time, s

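### Device status decides how closely the primary endpoint is watched, yet the AT comparison is stratified neither by it nor by the LA-diameter allocation factor

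*Protocol article*

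**What the plan says.** All references are to the protocol article.

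- **Endpoint.** Section 2.7.1: "The primary endpoint of this study is the occurrence of ATs at 1 year with a blanking period of 90 days after ablation". Section 2.5 defines the event: any documented AT "lasting ≥30 seconds occurring outside the blanking period of 90 days will be considered as a recurrence". The definition does not depend on the recording method.
- **Surveillance with a device.** Section 2.5: "In patients with cardiac implantable electronic device, home monitoring will be adapted to facilitate the continuous monitoring of AF episodes".
- **Surveillance without a device.** Section 2.5: one-channel "electrocardiograms will be recorded twice daily for 1 year after the procedure except for the blanking period of the 90 days".
- **Scheduled for patients generally.** Section 2.5 lists 12-lead ECGs, with clinic visits at 1 month and then every 1-3 months, and 24-hour Holters at 3, 12, 24 and 36 months.
- **Longer follow-up.** Section 2.7.2 makes AT occurrence at 3 years a secondary endpoint. The twice-daily recordings are specified only to 1 year.
- **Allocation.** Section 2.10 uses Pocock-Simon minimization "with a 1:1 allocation". One factor is named: "Randomization will be stratified by the LA diameter, which may influence the evaluation of the efficacy of the ablation procedure", split at 50 mm.
- **Analysis.** Section 2.12 says the log-rank "test will be used to compare the curves between the groups for the" time-to-event variables, with chi-square or Fisher tests for categorical ones. No stratification or covariate is stated, for device status or for LA diameter.
- **Baseline data.** Table 1 records device status (pacemaker, ICD, CRT-P, CRT-D). Section 2.8 lists interactions between ablation outcome and baseline patient characteristics.

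**The concern.** One event definition is applied to two surveillance systems of very different sensitivity. A patient with short or infrequent episodes is likely to be counted as a recurrence with a device and may well be counted as recurrence-free without one. Device status thus becomes a determinant of the recorded primary outcome, whichever ablation was given.

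The protocol's own reason for choosing LA diameter is that it may influence how efficacy is evaluated. Device status meets that description at least as directly, because it governs how efficacy is observed. It is nevertheless absent from both the allocation and the stated comparison.

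With 55 patients per arm, the arms can differ in device share by chance. The unadjusted comparison then carries variation that data already collected could remove. At 3 years the contrast in surveillance is wider still, because the twice-daily recordings have ended and the article states no such end for home monitoring.

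**Working it through.** **1. The plan's own figure.** Section 2.9 gives 51 per group for a two-sided 95% interval of total width 0.35 when both proportions are 0.20. With a continuity correction, the width at n = 51 is 2 × [1.96 × √(2 × 0.20 × 0.80 / 51) + 1/51] = 0.3497, so the 51 reproduces. The planned half-width is 17.5 points. With the allowance for loss, 55 per group are enrolled.

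**2. Surveillance coverage without a device, blanking to 1 year.**
- Window: 365 − 90 = 275 days = 6,600 hours.
- Strips: 2 × 275 = 550. At an assumed 30-60 seconds each (length not given), that is 4.6-9.2 hours.
- Holters at 3 and 12 months: at most 48 hours.
- Coverage: (4.6 + 48)/6,600 to (9.2 + 48)/6,600 = 0.8-0.9%.

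With a device, monitoring is described as continuous. Between months 12 and 36, the scheduled recordings without a device are two Holter days in 730 (0.27%), plus visit ECGs.

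Coverage is not the same as detection. Two strips a day catch a single, randomly timed 1-hour episode with probability 2 × 1/24 = 8%, and at least one of nine such episodes with probability 1 − (1 − 0.083)^9 = 54%. They catch a single 6-hour episode with probability 50%. If evenly spaced, they catch every episode of 12 hours or more. The article gives no distribution of episode lengths.

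**3. Chance imbalance in device share.** For device prevalence f, the SD of the difference between arms is √(2f(1 − f)/55). For f = 10-50% (assumed), the 95% limit is 1.96 × SD = 11-19 points.

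The resulting shift in the observed risk difference is the imbalance times d, the recorded recurrence rate with a device minus the rate without. Take 20% without a device and 30%, 40% or 50% with one (all assumed):

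| Recorded rate with a device | Shift at the 95% limit, f = 10-50% |
|---|---|
| 30% | 1.1-1.9 points |
| 40% | 2.2-3.7 points |
| 50% | 3.4-5.6 points |

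**4. What stratification recovers.** With overall recorded recurrence p, the share of the variance of the risk difference due to device status is f(1 − f)d² / [p(1 − p)].
- Smallest case, f = 0.10, d = 0.10, p = 0.21: 0.0009/0.1659 = 0.5%.
- Largest case, f = 0.40, d = 0.30, p = 0.32: 0.0216/0.2176 = 9.9%.

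**5. One case followed through.** Assume 40% with a device and recorded recurrence of 40% with a device and 15% without.
- p = 0.25, so the total variance is 0.25 × 0.75 = 0.1875.
- The device part is 0.4 × 0.6 × 0.25² = 0.015, or 8%.
- Unadjusted 95% half-width: 1.96 × √(2 × 0.1875/55) = 16.2 points.
- With the device part removed: 1.96 × √(2 × 0.1725/55) = 15.5 points.
- Shift at the 95% limit of imbalance: 1.96 × √(2 × 0.24/55) × 0.25 = 4.6 points.
- The parts add in quadrature: √(15.5² + 4.6²) = 16.2. The 4.6 points are already inside the unadjusted half-width.
- Type I error: in 200,000 simulated trials with no true effect and device share left to chance, the unadjusted two-sided 5% test rejected in 5.0%.

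**The case against.** The strongest reply is that randomization already deals with this. Surveillance follows a baseline characteristic, and the same schedule applies in both arms. Chance imbalance in device status is ordinary sampling variation that the unadjusted standard error already includes. This stands, and it rules out several stronger readings.

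- **A biased comparison.** A reader might infer that unequal monitoring tilts the result towards one ablation method. Nothing in the article links surveillance to arm, and the simulation shows no inflation of false positives.
- **An extra error of several points.** A reader might set the 4.6-point shift against the planned 17.5-point half-width and call it a quarter. That treats a component of the interval as if it came on top of it. Removing it narrows the half-width by only 0.7 points.
- **Device status ignored altogether.** Section 2.8 plans interactions with baseline characteristics, a set that includes device status through Table 1, and section 2.5 assesses AF burden in device patients. These exploratory items do not adjust the AT comparison, but a claim of no use at all would be wrong.
- **Only spot ECGs without a device.** Holters and visit ECGs are also scheduled, though they add little coverage.
- **Noninferiority made easier.** Missed events can shrink a true absolute difference, which matters in a design described as noninferiority. The article gives nothing from which to size this, and stratifying would not remove it.

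It can also be said that covariates are normally left to a fuller document. That is a fair reason to keep the point small. Still, the article does name the test, and the test as named leaves out the allocation factor.

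**Conclusion.** The point holds as an inexpensive improvement to the analysis. It is not a threat to validity. One recurrence definition is applied to continuous monitoring in some patients and to under 1% time coverage in the rest. The baseline variable that separates them enters neither the allocation nor the stated comparison, and the LA-diameter allocation factor is also absent from that comparison.

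The cost is about 0.5-10% of the variance of the risk difference, plus exposure to a chance device imbalance worth roughly 1-6 points at its 95% limit, which ordinary intervals already allow for. These figures rest on assumed device prevalence of 10-50% and assumed recorded recurrence of 30-50% with a device against 20% without. None of these splits is in the article. The pooled recurrence rate will also mix two sensitivities and depend on the share of device patients enrolled. The single 20% planning rate does not separate them. The mixture is likely to be more marked at 3 years.

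**What to change.** In section 2.12, state that the AT comparisons at 1 and 3 years are stratified by, or adjusted for, device status at baseline (yes/no) and LA diameter (<50 vs ≥50 mm). For the curves this is a stratified log-rank test. For a difference in proportions it is a stratum-weighted risk difference, for example with Mantel-Haenszel weights. Use device status as recorded in Table 1, so that a device implanted after randomization does not move a patient between strata. Report AT recurrence by arm within each device group, so that readers can see how far the pooled rate depends on the way patients were monitored.

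Both variables are already collected, so the cost is a sentence or two in the plan, fixed before outcome data are compared by arm. The downside is four strata in 110 patients, some of them small. If a stratum would hold very few patients or events, adjusting for the two factors as main effects in a model avoids the problem. No change to the minimization during enrolment is needed.

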### Sample size

2.9

The estimated sample size is 110 (55 in each group). The sample size was calculated based on the primary hypothesis. The recurrence rate of ATs after an ablation of AF has been reported to be comparable between the CB and RF ablation in patients without HF, ranging 65%‐90%,^11^, ^12^, ^19^, ^20^ and the recurrence rate of ATs after CB ablation in patients with HF with an LVEF ≤40% has been reported to be equal to those without HF.^21^ Therefore, we hypothesized that the incidence of recurrent ATs after an ablation procedure could be 20% in the AF patients from previous studies in both the CB and RF ablation groups. The sample size for the randomized comparison was calculated as 51 patients per group with a power of 80% by a two‐sided 95% confidence interval for the difference in the population proportions with a width that is equal to 0.35 when the two estimated group sample proportions are equally 0.20. To cope with a potential loss‐to‐follow‐up, a minimum of 55 patients per group will be enrolled in the study. Withdrawn patients will not be replaced.

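### Percentage change in AF burden is undefined for device patients with zero baseline burden, and the burden definition does not name the period summed

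*Protocol article*

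**What the plan says.** Section 2.5 (Follow-up) of the protocol article defines AF burden in one sentence. The numerator is "The sum of the durations of all episodes of ATs regardless of lasting ≥30 seconds or not". That sum "will be calculated and expressed as a percentage with respect to 24 hours to assess the AF burden", and the measure applies only to patients with an implanted device. For these patients the same section says that "home monitoring will be adapted to facilitate the continuous monitoring of AF episodes". It names no period for the sum, no rule for combining days and no baseline window.

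Section 2.8 (Other variables) lists both the absolute and the percentage change in AF burden at 1 and 3 years after ablation. AF burden appears neither in Section 2.7.1 (Primary endpoint) nor in Section 2.7.2 (Secondary endpoints).

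Section 2.6.1 (Inclusion criteria) requires at least one documented AF episode of 30 seconds or more and does not restrict the type of AF. Patients with little arrhythmia before ablation can therefore be enrolled.

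**The concern.** Two things stand out. First, a sum with no stated period is set against a fixed 24 hours, although the device records continuously. The sentence does not by itself tell an analyst what to compute.

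Second, and more important, percentage change divides by the baseline value. A device patient with no AT in the baseline window has no percentage change and leaves that analysis. The patients who remain were selected for having AT at baseline, so their burden tends to be lower on remeasurement even if ablation does nothing. At stake are the precision and the interpretation of the one listed rhythm variable that measures how much arrhythmia there is rather than whether it occurred.

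**Working it through.** The article states no figure for AF burden, so there is none to reproduce. Its inputs are a numerator of summed AT durations, a denominator of 24 hours, continuous device monitoring (all Section 2.5), and absolute plus percentage change at 1 and 3 years (Section 2.8). The share of days with AT, the length of the baseline window and the number of device patients are not given.

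**Step 1: what the definition yields.** Take a patient with 1 hour of AT per day over D days.

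- Sum over D days divided by 24 h: 100 × D/24. This gives 125% for D = 30 and 1521% for D = 365.
- Each day's AT time over 24 h, averaged over D days: 100 × D/(24 × D) = 4.17% for any D.

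The daily average cannot exceed 100%. If every day is fully monitored, it equals AT time divided by monitored time. It is the sensible reading, but the sentence does not state it.

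**Step 2: how often percentage change is undefined.** Percentage change = 100 × (follow-up − baseline)/baseline, which has no value when baseline = 0. Assume that a patient has AT on a share f of days and that days are independent. For a baseline window of W days, P(baseline = 0) = (1 − f)^W.

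| f | W = 1 day | W = 30 days |
|---|---|---|
| 5% | 95% | 21% |
| 10% | 90% | 4.2% |
| 25% | 75% | 0.02% |
| 50% | 50% | about 0% |

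The denominator does not enter this formula. A shorter window makes the problem more frequent, and no choice of denominator removes it.

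**Step 3: selection on a positive baseline.** Keep the same assumptions, give all patients the same f, and suppose that ablation has no effect. Let m be the mean burden on a day with AT.

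- Mean burden over all patients, at baseline and at follow-up: f × m.
- Mean baseline burden among patients with a positive baseline: f × m/[1 − (1 − f)^W].
- Apparent relative fall in mean burden among those patients: 1 − [1 − (1 − f)^W] = (1 − f)^W.

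The spurious fall in mean burden thus equals the probability in Step 2. For f = 5% it is 95% with a one-day baseline and 21% with a 30-day baseline. It arises in the same way in both arms.

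This concerns the change in mean burden. An average of individual percentages is also pulled upward by small positive baselines. Take f = 10% and W = 30, with the same burden on every AT day. The expected number of AT days is 3, and the mean of 1/(AT days) among patients with at least one is 0.428. The average individual change is then 3 × 0.428 − 1 = +28% with no true change. With one-day windows it is f − 1, for example −90% for f = 10%. The direction of error in that summary depends on the window, which is a further reason not to use it.

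**The case against.** The strongest reply is that this is a condensed sentence about a minor variable. Daily burden is a natural reading given continuous monitoring, and averaging windows and missing device days are details that an article may leave to the full protocol or analysis plan. That stands: the unnamed period alone would not justify a point.

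A reader might infer from the fixed 24-hour denominator that burden will exceed 100% for almost any recurrence, or else must be a single-day snapshot. The article does not support this. Section 2.5 counts a recurrence from 30 seconds, and one such episode is 30/86,400 = 0.035% of 24 hours. Passing 100% needs more than 24 hours of accumulated AT and a cumulative reading that is unlikely to be meant. The daily average is neither above 100% nor a snapshot.

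A reader might also infer that the CB versus RF comparison is biased. Nothing shows this. Exclusion depends on a value measured before ablation, so treatment does not drive it.

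Finally, Section 2.8 also lists absolute change, which can be computed from a zero baseline. That is true and limits the damage. It does not rescue percentage change, which Section 2.8 commits to explicitly rather than leaving open.

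**Conclusion.** The point holds at low severity. Percentage change in AF burden is a poor choice under any definition of burden, because patients with zero baseline cannot contribute. Their share could run from almost none to 95%, depending on the window length and the share of days with AT. Those figures rest on assumed values of f, independent days and, in Step 3, the same f for all patients. The article does not give the AF pattern or the number of device patients, so the actual loss cannot be estimated.

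The consequences are lost precision in a subgroup of the 110 planned patients and an overstated within-arm fall in mean burden among those retained. No primary or key secondary result is affected. The missing period is a wording gap that should be closed in the same edit.

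**What to change.** In Section 2.5, define AF burden as total AT time divided by total device-monitored time, leaving out time without device data. Use windows of one stated length: before ablation, ending at 1 year and ending at 3 years. In Section 2.8, replace absolute and percentage change with a between-arm comparison of absolute burden, or its rank, at each time point, adjusted for baseline burden. Drop percentage change. For device patients without pre-ablation recordings, report follow-up burden only.

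The cost is a few lines of wording, since device recordings are already part of follow-up. The downside is that percentage change in burden will no longer be reported.

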### Inclusion and exclusion criteria

2.6

#### Inclusion criteria

2.6.1

Subjects must meet all of the following criteria:
Diagnosed with HF with an LVEF ≤40%Diagnosed with AF with at least 1 episode documented (≥30 seconds) in accordance with the 2014 AHA/ACC/HRS guidelines^17^
Age 20‐85 yearsCapable of complying with the protocol and providing written informed consent.

#### Exclusion criteria

2.6.2

Those who meet any of the following criteria are ineligible for the study:
Previous catheter ablation and/or surgical procedure of AFLA diameter >55 mm (parasternal long‐axis view)Woman currently or possibly pregnantEnrollment in another investigational drug and/or device study.

